### Analysis and statistical methods

Intention to treat analysis will be used. The types of analysis proposed are Chi-square, generalized linear models, logistic regression and survival analysis, t-tests, ANOVA and non-parametric equivalents.

Analysis will be carried out at the end of the study, as there is likely to be insufficient power for interim analyses. Quality control of data collection will be conducted by a trial management committee throughout the study and by a statistician independent of the research team.

Logistic regression would be used to relate D-dimer result and other patient data to events such as recurrence, bleeding episodes and PTS separately on the two arms (Group W and Group O) of the trial and together. Baglin *et al*[10], with their 272 patients, showed a significant association between age and D- dimer (p < 0.001) and our total sample, allowing for loss to follow up, of 316 should be ample to incorporate such a relationship. In comparing D-dimer levels between genders they achieved a significance level of p = 0.18 with 272 individuals. A rough calculation would suggest a p value of 0. 15 for the same level of difference in D-dimer (approximately 80 ng/ml) in our total sample of 316 patients.

#### Cost effectiveness analysis

The analysis will determine the cost-effectiveness of the measurement of D-dimer and subsequent extended treatment with anticoagulation. Data collection will be for all trial patients so that a stochastic cost analysis can be undertaken. A cost-consequence analysis will initially be reported, describing all the important results relating to costs and consequences. Subsequently, a cost-effectiveness analysis will be conducted using data on the clinical events of interest (thrombotic and bleeding events). An incremental analysis will be undertaken to calculate the cost per major outcome averted. A cost-utility analysis will also be undertaken using patient responses to the EQ-5D questionnaire, to calculate the cost per additional Quality-Adjusted Life Year (QALY) gained.

The analysis will be from an NHS perspective, however patient costs will be incorporated in a sensitivity analysis in order to consider cost-effectiveness from a broader perspective. The data for costs is likely to have a skewed distribution therefore the plan is to explore the nature of the distribution of costs. If the data is not normally distributed, the non parametric comparison of means (e.g. bootstrapping) will be undertaken. Efforts will be made to minimise the problem of missing data, but if this does pose a problem at the economic analysis stage then imputation techniques will be used.

In addition to the trial-based economic evaluation, longer term costs and consequences will be explored by extrapolating beyond the end of the trial. Decision modelling will be undertaken using data from the trial and from non-trial sources, in order to determine the long-term cost-effectiveness of the intervention, with results reported as cost per additional QALY gained.

The robustness of the results will be explored using sensitivity analysis. This will explore uncertainties in the trial based data itself, the methods employed to analyse the data and the generalisability of the results to other settings. Uncertainty in the confidence to be placed on the results of the economic analysis will be explored by estimating cost effectiveness acceptability curves. These plot the probability that the intervention is cost effective against threshold values for cost effectiveness.

#### Data validation

Data cleaning will take place by a series of logical checks on the electronic data using specific queries. Discrepant data entries will be checked with the source documents and the database amended if necessary.

#### Data management, protection and confidentiality

The data management is fully compliant with the Data Protection Act and ICH GCP. The trial is registered with Legal Services at the University of Birmingham who are responsible for ensuring that the purposes for which the University processes personal data is registered with the Information Commissioners office.

Submissions will be made to the NHS IC Medical Research Information Service for flagging deaths, exits from and re entries to the NHS, including PCT data.

### Time plan

It is anticipated that patient recruitment will take place over a 2 year period. Patient follow-up will then continue for a further 2 years.

### Assessment of safety

Participants safety will be ensured by screening for eligibility using a structured form completed by trial healthcare professionals. This will record evidence of eligibility and the presence/absence of any inclusion and exclusion criteria. The Research Associates and Nurses will take a general medical and drug history to assess for other complicating diseases and medications. Any queries will be discussed with the trial nurse, chief investigator and the relevant physicians at the trial site. The eligibility will be signed off by the physician providing routine medical care.

### Adverse event reporting

Data will be collected for all serious adverse events (SAE), non-serious adverse reactions (NSAR), serious adverse reactions (SAR) and SUSAR as defined in Table 3. Adverse events (AEs), SAEs and suspected unexpected serious adverse reactions (SUSARs) will be reported in compliance with International Conference on Harmonisation (ICH)- Good Clinical Practice (GCP) Guidelines.

**Table 3 T3:** Definition of adverse events

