### Trial intervention

Study participants will have a total of six visits over a two year period.

#### Visit 1

This is the same visit as the information, consent and randomisation visit and will be within 2 weeks of current anticoagulation treatment end date. Patients will be randomised electronically into one of two groups; Group O will discontinue warfarin after their usual clinical intervention, Group W will continue warfarin for a further two years.

Patients will be interviewed to collect the following data:

Concomitant medications; ethnicity; smoking status; alcohol consumption; medical history; BMI; and family history of VTE

A heparinised venous sample of blood will be taken for a D-dimer test on a POC device (Cobas h 232, Roche diagnostics). In addition citrated venous samples will be collected for D-dimer testing. These will be sent to a central laboratory to be frozen and stored for analysis during and at the end of the study.

The D-dimer result will be recorded centrally onto a database for future analysis and both patient and researcher will be blinded as to the result of this test.

All patients will be clinically examined for signs and symptoms of PTS using a validated clinical scoring system (the Villalta scale) and will also complete the VEINES quality of life score [24] as well as EQ 5D which allows the measurement of broad aspects of quality of life [25]. In addition the patients will complete a costs questionnaire relating to the expenses incurred on a recent anticoagulation clinic visit. Where questionnaires are incomplete or unclear the patients will be contacted by telephone to clarify and complete the responses.

Compression stockings will be used by patients as advised by the clinician treating the DVT and the researchers will not influence their utilisation.

The anticoagulation clinic that the patient would normally attend will be informed that the patient is entering a study as will any specific hospital consultants who are involved with the patients’ care (e.g. haematologists). Patients randomly allocated to Group W will be followed-up through their usual oral anticoagulation service provided in terms of warfarin management and the anticoagulation clinic lead will be asked to extend their clinic visits for a further 2 years. Patients randomly allocated at this point to Group O will undergo a further D-dimer test 1 month after cessation of treatment. Again both researcher and patient will be blinded to this result.

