#### Visits 2–6

All patients randomised (Groups W and Group O) will be reviewed every 6 months for 2 years in total to assess evidence of VTE recurrence, clinical assessment of PTS, and measurement of D-dimer (again patient and researcher are blinded to these results).

All patients will again be asked to complete the VEINES-QOL/Sym a validated disease specific, quality of life score, and EQ 5D, questionnaires.

If a patient in Group O (off warfarin) has their warfarin restarted by their GP during the study period for a VTE recurrence then they will be removed from the study but a case review will be carried out in patient’s primary care notes looking for evidence of thrombotic events. If a patient in Group O has to restart warfarin for another reason e.g. atrial fibrillation, then they will continue to be followed up in the usual manner. If a patient in Group W (on warfarin) has to permanently stop taking their warfarin during the study then they will be followed up and included in the final analysis on an intention to treat basis. If a patient in Group W has a temporary break in their treatment for any reason, they will continue to follow the same visit regime, making a note of the temporary break.

Patients in Group W will be asked to return for a final D-dimer test 1 month after discontinuing warfarin.

Patients randomised into group W will continue with their warfarin management as before. INR data will be collected from the anticoagulation database at six monthly intervals throughout the study to assess overall control.

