#### Secondary outcomes

1. Severity of PTS between groups

2. Bleeding events - defined as in Table 2

3. INR control in terms of percentage time in range

4. Optimal cut off on a D-dimer result

5. Costs of D-dimer and subsequent extended treatment with anticoagulation

6. Cost effectiveness

7. Information on the types of patient who potentially benefit from extended warfarin treatment, age and gender

8. Patient quality of life

**Table 2 T2:** Definition of bleeding events

**Major bleeding**	Clinically overt bleeding that is associated with:
	A fall in haemoglobin of 2 g/dl or more, or
	A transfusion of 2 or more units of packed red blood cells or whole blood, or
	A critical site: intracranial, intraspinal, intraocular, pericardial, intra-articular, intramuscular with compartment syndrome, retroperitoneal, or
	A fatal outcome
**Non-major clinically relevant bleeding**	Non-major clinically relevant bleeding is defined as overt bleeding not meeting the criteria for major bleeding but associated with medical intervention, unscheduled contact (visit or telephone call) with a clinician, (temporary) cessation of warfarin treatment, or associated with discomfort for the subject such as pain or impairment of activities of daily life.
	Examples of non-major clinically relevant bleeding are:
	• Epistaxis if it lasts for more than 5 minutes, if it is repetitive (i.e., 2 or more episodes of true bleeding, i.e., not spots on a handkerchief, within 24 hours), or leads to an intervention (packing, electrocautery, etc.) and no admission to hospital.
	• Gingival bleeding if it occurs spontaneously (i.e., unrelated to tooth brushing or eating), or if it lasts for more than 5 minutes
	• Haematuria if it is macroscopic, and either spontaneous or lasts for more than 24 hours after instrumentation (e.g., catheter placement or surgery) of the urogenital tract
	• Macroscopic gastrointestinal haemorrhage: at least 1 episode of melena or hematemesis, if clinically apparent
	• Rectal blood loss, if more than a few spots
	• Haemoptysis, if more than a few speckles in the sputum, or
	• Intramuscular hematoma
	• Subcutaneous hematoma if the size is larger than 25 cm^2^ or larger than 100 cm^2^ if provoked

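### The between-arm comparison of non-major bleeding is at risk of bias against Group W: one qualifying criterion, the collection label and clinic contact all favour counting bleeds in patients on warfarin

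*Protocol article*

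**What the plan says.** - **Outcome.** The protocol's second secondary outcome is "Bleeding events - defined as in Table 2". Table 2 divides bleeding into major and non-major clinically relevant.
- **Major bleeding.** The definition opens "Clinically overt bleeding that is associated with" and continues with a haemoglobin fall, transfusion, a critical site or death. None of these refers to warfarin.
- **Non-major bleeding.** This is an overt bleed, not major, that meets any one of four alternatives. The first is medical intervention. The other three are: "unscheduled contact (visit or telephone call) with a clinician, (temporary) cessation of warfarin treatment, or associated with discomfort for the subject". Table 3 repeats the wording as the definition of a non-serious adverse reaction.
- **Collection.** The section on adverse event reporting states: "Data will be collected for all serious adverse events (SAE), non-serious adverse reactions (NSAR), serious adverse reactions (SAR) and SUSAR as defined in Table 3". The next sentence says that adverse events are also reported, in line with ICH-GCP.
- **Contact.** For Group W, "the anticoagulation clinic lead will be asked to extend their clinic visits for a further 2 years". Group O has no counterpart. Both arms have six-monthly reviews, whose stated purpose is "to assess evidence of VTE recurrence, clinical assessment of PTS, and measurement of D-dimer".
- **Adjudication.** Under Ascertainment of outcomes, a committee blinded to allocation decides the primary cause of hospitalisation or death.
- **Use.** The statistical section relates bleeding episodes to D-dimer and other patient data by logistic regression, in each arm and in both together. The cost-effectiveness analysis uses thrombotic and bleeding events.

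**The concern.** The Background gives bleeding as the reason for caution about prolonged warfarin, so bleeding is the harm to be set against fewer recurrences. A fair comparison needs a bleed to have the same chance of being counted in either arm. The protocol describes blinding of the D-dimer results and of the event committee, but not of treatment. Definition and ascertainment therefore have to supply the balance. For non-major bleeding they lean one way, towards counting more in Group W. Any such lean would add to the excess bleeding attributed to extended treatment.

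**Working it through.** The protocol states no bleeding rate and no power for bleeding, so there is no figure of its own to reproduce. The check is a reading of the definitions, followed by an illustration.

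**Step 1: criteria by arm (Tables 2 and 3)**

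| Criterion | Group W | Group O, off warfarin |
|---|---|---|
| Major: haemoglobin fall, transfusion, critical site, death | open | open |
| Non-major: medical intervention | open | open |
| Non-major: unscheduled clinician contact | open | open |
| Non-major: stopping warfarin, even temporarily | open | closed |
| Non-major: discomfort or impairment | open | open |

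One of the four non-major criteria is closed to Group O. It matters only for bleeds that qualify by that criterion alone.

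**Step 2: label.** Serious adverse events are defined without any need for a causal link to treatment, so a Group O bleed that meets those criteria is captured. Non-major bleeding appears in Table 3 only as a reaction. Table 3 sets no causality condition on that term, but in ordinary use a reaction is a response to a drug. A site could therefore leave out a minor bleed in a patient taking none.

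**Step 3: chance of notice.** Both arms have the six-monthly reviews, and Group W has two further years of anticoagulation clinic visits. Most non-major bleeds would not involve admission or death, so the blinded committee would not rule on them.

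**Step 4: illustration.** The inputs are:
- n = 158 per arm, from the Sample size section: 316 completing / 2, taking equal arms.
- p = true two-year risk of non-major bleeding, the same in both arms. **Assumed**, 5% to 15%.
- s = share of Group O events not counted, with full capture in Group W. **Assumed**, 5% to 30%.

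Spurious difference d = p − p(1 − s) = ps. Spurious risk ratio = 1/(1 − s).

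Chance that a two-sided 5% test declares Group W worse = Φ[(d − 1.96·SE0)/SE1]. SE0 is the pooled and SE1 the unpooled standard error. The nominal value is 2.5%.

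Example with p = 10% and s = 20%:
- d = 0.10 × 0.20 = 0.02
- SE0 = √(2 × 0.09 × 0.91/158) = 0.0322
- SE1 = √((0.10 × 0.90 + 0.08 × 0.92)/158) = 0.0322
- (0.02 − 1.96 × 0.0322)/0.0322 = −1.34, and Φ(−1.34) = 9.0%

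Results for p = 10% (158 × 0.10 = 15.8 events in Group W):

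| s | Counted in Group O | Difference | Risk ratio | False finding that W is worse |
|---|---|---|---|---|
| 5% | 15.0 | 0.5 points | 1.05 | 3.5% |
| 10% | 14.2 | 1.0 points | 1.11 | 4.9% |
| 20% | 12.6 | 2.0 points | 1.25 | 9.0% |
| 30% | 11.1 | 3.0 points | 1.43 | 15.7% |

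Over p of 5% to 15% and s of 5% to 30%, the spurious difference runs from 0.25 to 4.5 points and the false-finding rate from 3.2% to 22.3%. The risk ratio depends only on s, which the protocol does not inform.

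**The case against.** The case against is substantial.

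- **Most of the definition is neutral.** Three of the four non-major criteria are open to Group O. The listed examples, such as a prolonged nosebleed or a large haematoma, do not depend on warfarin. A bleed that leads to stopping warfarin will often also involve clinician contact. This stands, and it confines the definitional problem to bleeds that qualify solely by cessation. How many there would be is unknown.
- **The label need not mislead.** The protocol collects reactions as Table 3 defines them, and that definition has no causality test. Adverse events are also said to be reported. This stands as a reading of the text. What remains is ambiguity: a site may take the label at its ordinary meaning, and nothing tells it not to.
- **Bleeding data are planned for everyone.** The Cost data section collects bleeding events at patient level, the economic analysis covers all trial patients, and the regression uses both arms. This stands. It shows an intention to collect in both arms, but it does not set a common enquiry or an arm-neutral definition.
- **The visit summary proves little.** A reader might infer that nobody asks Group O about bleeding, because the six-monthly review does not list it. A condensed article does not support that; the full protocol or the case report form may contain the question.
- **Clinic contact is partly inference.** The article describes INR and warfarin-dose data passing from the anticoagulation service to the trial, not reports of bleeding. Extra contact gives more chance for a bleed to be noticed, but the route into the trial data is not stated.

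**Conclusion.** The point holds as a risk of bias against Group W in one component of a secondary outcome, non-major clinically relevant bleeding. It rests first on a stated rule: a qualifying criterion that a Group O patient off warfarin cannot meet. The reaction label, the extra clinic contact and the limited scope of blinded adjudication add to it in the same direction.

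The size cannot be computed from the protocol. The ranges in the working rest on assumed bleeding rates, equal true risk and assumed under-counting.

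Two stronger readings should be resisted:
- **That the bleeding comparison as a whole is biased.** Major bleeding is defined neutrally, and serious events are collected regardless of cause.
- **That the bias can be put at a risk ratio of, say, 1.25 to 2.0.** That range only restates an assumed capture of 80% to 50% in Group O (1/0.8 and 1/0.5). Nor does the protocol show that non-major bleeds enter the cost per major outcome averted, so a distortion of that result is not established.

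No stated sample size or power figure changes.

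**What to change.** Make three changes, all on existing visits and forms:

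1. For the between-arm comparison, count non-major bleeds only by criteria that both arms can meet. Report bleeds that qualify solely by stopping warfarin separately, as a description of Group W.
2. Record every overt bleed as an event in both arms, whatever its judged causality.
3. Ask the same question about bleeding at each six-monthly visit and GP-record review in both arms. If the full protocol already has this, say so in the outcome section.

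The cost is one form question and a reworded collection rule. The downsides are a few more non-serious events to record in Group O and slightly less comparability with studies that use the unmodified definition. Reporting the cessation-only bleeds separately lets the unmodified Group W count be recovered.

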	**A fatal outcome**
**Definition of serious adverse reaction**	Any thrombotic event e.g. stroke, TIA
	Major Bleeding- Defined as clinically overt bleeding that is associated with:
	• A fall in haemoglobin of 2 g/dl or more, or
	• A transfusion of 2 or more units of packed red blood cells or whole blood, or
	• A critical site: intracranial, intraspinal, intraocular, pericardial, intra-articular, intramuscular with compartment syndrome, retroperitoneal, or
	• A fatal outcome
**Definition of a non serious adverse reaction**	Defined as overt bleeding not meeting the criteria for major bleeding but associated with medical intervention, unscheduled contact (visit or telephone call) with a clinician, (temporary) cessation of warfarin treatment, or associated with discomfort for the subject such as pain or impairment of activities of daily life.
	Examples of non-major clinically relevant bleeding are:
	• Epistaxis if it lasts for more than 5 minutes, if it is repetitive (i.e., 2 or more episodes of true bleeding, i.e., not spots on a handkerchief, within 24 hours), or leads to an intervention (packing, electrocautery, etc.) and no admission to hospital.
	• Gingival bleeding if it occurs spontaneously (i.e., unrelated to tooth brushing or eating), or if it lasts for more than 5 minutes
	• Haematuria if it is macroscopic, and either spontaneous or lasts for more than 24 hours after instrumentation (e.g., catheter placement or surgery) of the urogenital tract
	• Macroscopic gastrointestinal haemorrhage: at least 1 episode of melena or hematemesis, if clinically apparent
	• Rectal blood loss, if more than a few spots
	• Haemoptysis, if more than a few speckles in the sputum, or
	• Intramuscular hematoma
	• Subcutaneous hematoma if the size is larger than 25 cm^2^ or larger than 100 cm^2^ if provoked
**Definition of serious adverse event**	A serious adverse event is defined as an untoward medical occurrence in a participant of a study that does not necessarily have a causal relationship with the treatment that results in:
	• Death,
	• Is life threatening
	• Requires hospitalisation or prolongation of existing hospitalisation
	• Results in persistent or significant disability or incapacity
	• Consists of a congenital abnormality or birth defect
	Other known rare adverse reaction listed in the SmPC are:
	Skin reactions: Purpura and ecchymosis
	Pruritic lesions
	Skin necrosis
	Alopecia
	Diarrhoea
	An unexplained fall in haematocrit
	Jaundice and hepatic dysfunction
	Fever, nausea, vomiting and pancreatitis
	Hypersensitivity reactions are extremely rare and if any of these reactions occur they will be reported and it will be recommended to the clinician responsible for the participants warfarin management that warfarin is replaced by an alternative anticoagulant drug
	A thrombotic event can also be defined as a serious adverse event related to warfarin.

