## Methods

### Aims and objectives

Considering patients with a first unprovoked proximal DVT and PE who have been treated with 3–6 months oral anticoagulation, the aims of the study are:

•To investigate the effect of extending treatment with oral anticoagulation in terms of reduction in incidence of VTE and PTS

•To develop an algorithm to predict high/low recurrence rates in these patients

As part of this we will be investigating the following:

•To establish the performance characteristics of D-dimer testing whilst still on treatment as a prediction tool for recurrence of VTE in patients with first unprovoked proximal DVT or PE.

•To establish factors which contribute to the recurrence of VTE in patients with a first unprovoked proximal DVT or PE.

•To determine the cost-effectiveness of the measurement of D-dimer and subsequent extended treatment with anticoagulation.

•To determine patient preferences and utilities with regard to extended warfarin treatment.

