### Outcome measures

#### Primary outcomes

1. Number of recurrent thrombotic events between those with raised D-dimer at point of randomisation who were randomly allocated to the treatment arm (group RW) and those with raised D-dimer at point of randomisation who were randomly allocated to the no treatment arm and produced a normal D-dimer off treatment (NRO) and those with raised D-dimer at point of randomisation who were randomly allocated to the no treatment arm and then produced a raised D-dimer off treatment (RRO) (see Figure 1)

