**Figure 1 F1:**
[figure not shown]
Flow chart for trial intervention.

2. Number of recurrent thrombotic events between those showing an elevated D-dimer off treatment (RO) versus those showing a negative D-dimer off treatment (NO) (see Figure 1)

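### Table 3 makes every thrombotic event a serious adverse reaction whatever the arm, exposure or cause, so primary-outcome recurrences in patients assigned to stop warfarin are recorded as reactions

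*Protocol article*

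**What the plan says.** Under *Adverse event reporting*, the protocol article says that data will be collected for "serious adverse reactions (SAR) and SUSAR as defined in Table 3", among other categories. Table 3 is therefore the working definition for safety data in both arms.

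In Table 3 the first entry under serious adverse reaction is "Any thrombotic event e.g. stroke, TIA", followed by major bleeding. No condition on arm, drug exposure or assessed cause is attached. By contrast, the same table describes a serious adverse event (SAE) as one that "does not necessarily have a causal relationship with the treatment". The table ends with the sentence "A thrombotic event can also be defined as a serious adverse event related to warfarin".

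Under *Trial intervention*, "Group O will discontinue warfarin after their usual clinical intervention". The first item under *Primary outcomes* begins "Number of recurrent thrombotic events between those with raised D-dimer at point of randomisation", and the second also counts recurrent thrombotic events. The aim is put as the effect of extended treatment "in terms of reduction in incidence of VTE and PTS".

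**The concern.** A reaction, as opposed to an event, is a harm attributed to the treatment. Table 3 itself draws that line, because it frees only the SAE from a causal link. Placing all thrombotic events on the reaction side settles attribution by definition. In this trial that goes wrong in one arm in particular: Group O patients are assigned to stop the drug, and a recurrence is the failure that warfarin is meant to prevent. The same event then serves as evidence of benefit in the efficacy analysis and as a serious reaction in the safety data.

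What is at stake is whether the SAR data can be interpreted. If they are set out by arm, the count for the arm that stops warfarin will consist largely of efficacy failures, and the count for the warfarin arm will mix these with bleeding. Table 3 also gives one event two labels, SAR in one row and warfarin-related SAE in the closing sentence, so sites could classify like cases differently.

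**Working it through.** **Inputs, all from *Sample size*.** Two-year recurrence of 21.4% against 4.3% in D-dimer-positive patients; 14.2% in the no-treatment arm overall; 1.4% to 4.3% in the warfarin arm overall; 316 completers, hence 316 / 2 = 158 per arm; 5% significance and 90% power.

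**Step 1: reproduce the plan's figures.** Two proportions, two-sided, pooled variance under the null, no continuity correction:

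n = [z(0.975) √(2 p̄(1 − p̄)) + z(0.90) √(p1(1 − p1) + p2(1 − p2))]² / (p1 − p2)²

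With p1 = 0.214, p2 = 0.043 and p̄ = 0.1285:

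- (1.960 × 0.4733 + 1.282 × 0.4576)² / 0.171² = 78.4, so 79 per group, as stated.
- 79 × 4 = 316 and 316 / 0.9 = 351.1, in line with the stated 352.
- Power at 158 per arm is 86.3% for 14.2% v 4.3% and 99.1% for 14.2% v 1.4%, matching the stated 86% to 99%.

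The rates can therefore be used as the plan uses them. Nothing here changes the sample size.

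**Step 2: expected recurrences that Table 3 would label SARs (n × rate).**

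| | Group O | Group W | Share in Group O |
|---|---|---|---|
| All completers, W at 1.4% | 158 × 0.142 = 22.4 | 158 × 0.014 = 2.2 | 22.4 / 24.6 = 91% |
| All completers, W at 4.3% | 158 × 0.142 = 22.4 | 158 × 0.043 = 6.8 | 22.4 / 29.2 = 77% |
| D-dimer positive, 79 v 79 | 79 × 0.214 = 16.9 | 79 × 0.043 = 3.4 | 16.9 / 20.3 = 83% |

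**Step 3: what this would do to a SAR table by arm, if one were made.** Recurrences alone put Group O ahead by 22.4 − 6.8 = 15.6 to 22.4 − 2.2 = 20.2 events. Major bleeds in Group W would have to outnumber those in Group O by about 16 to 20 (10 to 13 percentage points of 158) before such a table showed more reactions in the warfarin arm. This needs no assumed bleeding rate. It takes each recurrence as one SAR and leaves arterial events out.

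**Step 4: arm is not exposure.** *Visits 2–6* provides for Group O patients who restart warfarin and Group W patients who stop it permanently. A correct definition of reaction must therefore rest on exposure at the time of the event, not on the allocated arm.

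**The case against.** The strongest case for leaving the text alone is that nothing stated in the plan depends on it.

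- **Bleeding.** It is a separate secondary outcome under Table 2, which contains no thrombotic events. A reader might infer that the SAR definition would reverse the bleeding comparison between the arms. The document does not support that: bleeding would be reported on its own, and no section says SARs will be totalled or compared by arm.
- **Safety board.** A reader might infer that the board would be misled by a pooled tally. The only board task described is to report low recruitment, and analysis is planned at study end without interim looks.
- **Arterial events in the primary outcome.** Because stroke and TIA are the examples given, a reader might infer that they count towards it. The wording is *recurrent* events in patients with a first DVT or PE. The aims and the six-monthly visits refer to VTE, recurrence must be documented radiologically with criteria given for DVT, and Table 3 governs safety reporting only. The endpoint is evidently venous; the word is merely missing from the two primary outcomes.
- **Wording and format.** The closing sentence of Table 3 says *can*, so it is permissive, and the SAR row does not itself name warfarin. The full protocol may also hold a causality procedure that the article omits.

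The first three points stand and limit the finding to safety classification. The last stands only in part. The SAR row is not permissive, it is the definition under which data are collected, and its contrast with the SAE row gives it a causal meaning. A causality procedure elsewhere would conflict with a rule that assigns the category by event type, so this is a matter of what the article states and not of what it leaves out.

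**Conclusion.** The point holds as a misclassification of safety events. As written, a recurrence in Group O is at once the primary-outcome event and a serious adverse reaction in a patient assigned to stop the drug. About 22 events in Group O against 2 to 7 in Group W would be so labelled, 77% to 91% of them in Group O.

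These figures rest on the protocol's planning rates, on 158 completers per arm and on a literal reading of Table 3. They are expected counts by allocated arm; restarts and stops of warfarin would move some events between exposed and unexposed time. No bleeding or stroke rate is given in the document and none is needed for this conclusion.

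The consequence is confined to the SAR data: any tabulation by arm would mix lack of efficacy with harm. The primary comparison, the bleeding outcome, the power and the sample size stand as they are. The definition should be corrected, but the error does not threaten the trial's main result.

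**What to change.** Reconcile Table 3 with *Primary outcomes* and *Thrombotic events and associated deaths*:

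1. Remove thrombotic events from the serious adverse reaction row and delete the closing sentence of Table 3 on thrombotic events related to warfarin.
2. Record recurrent VTE as an efficacy endpoint. A recurrence that meets a seriousness criterion still falls under the SAE definition, which needs no causal link, so no such event is lost.
3. Record stroke, TIA and other arterial events as SAEs, assess causality case by case, and tabulate them by arm.
4. Limit *reaction* to events in patients exposed to warfarin, judged by actual exposure rather than allocation.
5. As a minor clarification, word both primary outcomes as recurrent VTE (DVT or PE), in line with the aims and the visit assessments.

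The cost is an edit to Table 3 and the two primary outcomes, and matching event categories on the case report form. No new data are needed and the sample size does not change.
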